## Abstract

**Background:**

Intellectual disability (ID) is characterized by limitations in intellectual functioning and adaptive behavior. Adults with ID exhibit higher rates of obesity and poorer health status compared to the general population. Continuity of care and barriers to health-related activities may contribute to the poorer health status observed in this population. To address this problem, a tailored weight management online health information and communication technology platform, known as POWERS_f*orI*D_, was developed and is being tested to determine if this delivery mechanism can improve weight maintenance/weight loss in adults with ID.

**Methods:**

Obese adults with mild-to-moderate ID (n = 70) are randomized to the POWERS_*for*ID_ intervention or control group for a 24-week trial. Each group undergoes an assessment that includes body weight, waist circumference, and percent body fat at baseline and at weeks 6, 12, and 24. Physical activity barriers, healthy eating barriers, food frequency, and psychosocial wellbeing are measured at baseline and at weeks 12 and 24. Blood lipids are assessed at baseline and 24 weeks. Participants randomized to POWERS_*for*ID_ receive access to the POWERS_*for*ID_ website and calls from a health coach (weekly during weeks 1–12, biweekly during weeks 13–24). The health coach employs motivational interviewing techniques adapted for individuals with ID to promote behavior change. Participants randomized to the control group receive standard clinical weight-loss care. Differences in weight, waist circumference, blood lipids, percent body fat, and psychosocial self-report will be assessed. Barriers and facilitators of implementation as well as perception of study outcomes will be conducted via qualitative analysis.

**Discussion:**

POWERS_*for*ID_ is a novel information and communication technology platform designed to address health needs for adults with ID. This article describes the development and components of POWERS_*for*ID_. The overall aim is to assess usability and feasibility of POWERS_*for*ID_ for promoting weight loss for obese adults with ID over the course of a 24-week randomized control trial.

**Trial registration:**

Clinicaltrials.gov, NCT03139760. Registered on XXX

**Electronic supplementary material:**

The online version of this article (doi:10.1186/s13063-017-2239-2) contains supplementary material, which is available to authorized users.

## Background

Intellectual disability (ID) is characterized by significant limitations in intellectual functioning (IQ of 75 or less) and adaptive abilities, such as conceptual, social, and practical skills. An individual may be diagnosed with ID after assessment via standardized test batteries and structured interviews. Classifications of ID include mild (IQ 50–69), moderate (IQ 35–49), or profound [1]. Individuals with ID are more likely to be overweight or obese, have poorer health status, and limited access to health promotion programs compared to the general population [2–7]. The consequences of obesity predispose adults with ID to a greater risk of secondary health conditions that can impair their health status and quality of life [8]. Lack of healthy eating habits and regular physical activity may be associated with the higher rate of obesity seen in this population [9, 10]. However, current approaches to creating healthier lifestyles (i.e. improved nutrition and increased physical activity) for adults with ID can be extremely challenging because of many different barriers including financial constraints to join a fitness facility, transportation issues, limited choices, and the need for greater involvement and support from caregivers [11–15].

The current healthcare delivery system for adults with ID provides little guidance in health promotion to families or developmental disability service providers. As a result, many if not most individuals and care providers/families are unprepared to manage or improve weight management for people with ID [12]. General recommendations to get more exercise or eat better (e.g. restrict caloric intake, consume more fruits and vegetables, etc.) are often ineffective, particularly in populations where there are interactions between the environment, living arrangements, and supervised care. Compared to people without ID, people with ID experience much poorer continuity of care and health maintenance including receiving fewer routine and preventive health services such as blood pressure checks and cholesterol and cancer screenings [16]. Thus, few clinically successful weight-loss studies have been reported in the ID literature.

Individuals with ID and caregivers may be able to benefit from a tailored health information and communication technology (ICT) infrastructure that would allow greater continuity among staff and families in tracking and managing obesity in adults with ID. Online physical activity and nutrition guidance systems hold promise in assisting with recognition of what barriers must be overcome and strategies developed to reduce obesity rates in adults with ID [12]. ICT systems also allow for increased monitoring, one of the key elements of managing and reducing body weight [17, 18]. Likewise, these new technologies provide an opportunity to promote consistent healthcare delivery to individuals with ID, as they are using Internet and communication devices at rates similar to the general population [19].

To our knowledge, only one study incorporated the use of technology to assist with achieving weight loss in individuals with ID [20]. Researchers provided study participants with tablet computers for two months to assist with tracking physical activity, dietary intake, and video conference with a registered dietitian. On average, participants used the tablet for tracking dietary intake on 83% of days during the two-month period and lost 3–4% of body weight. The results of the study indicate the feasibility of individuals with ID to use ICT for health-related behaviors.

To date, there are no randomized controlled trials examining the effectiveness of a weight-loss program using ICT and motivational interviewing in obese adults with ID. Given the complex health needs and extreme fragmentation of healthcare delivery experienced by adults with ID, there is a strong and growing need to develop a scalable health IT system that can support the diverse needs of adults with ID. Therefore, the aim of this paper is to describe the design of a blended online health promotion intervention using an innovative e-Health platform that has been designed specifically for adults with ID to reduce modifiable clinical, anthropometric, and behavioral risk factors associated with obesity.

## Methods/Design

The intervention presented in this manuscript is based on two previous studies that reported successful weight loss using an online ICT weight management system with remote access to a health coach to reduce obesity in adults with physical disabilities and chronic health conditions [21, 22]. Results indicated statistically significant weight loss in both studies in the range of 3–7% [21, 22]. The system, referred to as POWERS (Personalized Online Weight and Exercise Response System), is a novel, multifocal-centered tailored intervention utilizing an innovative online tool designed to facilitate improvements in physical activity and nutritional behaviors.

The POWERS interface has been adapted to address the specific needs of adults with ID and their caregivers. In addition, health coaching with motivational interviewing (MI) techniques was adapted for this population [23]. The description of the study protocol follows the SPIRIT 2013 checklist, CONSORT statement for randomized trials, and TIDieR checklist for intervention description and replication [24–26].

### Study objectives

The overall study objective is to assess the usability, feasibility, and outcomes of a personalized online remote weight-management MI coaching system designed for use with adults with ID, which is referred to as POWERS_*for*ID_. The steps taken to achieve this overall objective include: (1) assessment of the acceptability and usability of the POWERS system for individuals with ID; (2) adaptation of the POWERS system based on qualitative feedback from participants, caregivers, and research staff; and (3) development of a randomized controlled trial (RCT) to examine the effect of POWERS_*for*ID_ on health status and body weight in obese adults with ID when compared to usual care.

### Setting and target population

Individuals with mild or moderate intellectual disability residing in and around Colorado Springs, CO, USA who receive healthcare services from a clinic specializing in developmental disabilities are eligible for the study. Only patients diagnosed with intellectual or developmental disability (IDD) are enrolled at the clinic. The clinic’s medical team determines patient eligibility to enroll at the clinic based on a diagnosis of an intellectual or developmental disability after reviewing available patient records (e.g. medical history, psychological evaluation, school records, developmental disability determination form, etc.). If patient records are limited or unavailable, then clinic staff providers perform medical evaluations to determine eligibility to enroll in the clinic. Eligibility to participate in the study is partially determined by the investigator’s observation of the individual’s functional skills (e.g. communication, ability to follow instructions with assistance, ability to use a computer with assistance, etc.). Ethical permission was obtained through the Institutional Review Board at a major university associated with the study design. All participants provide informed consent before participating. Eligible participants reside in either a group home, host home, family home, or independently. In compliance with ethical guidelines, participants without a legally authorized representative are also included. Individuals with ID who meet the following criteria are eligible for the study: (1) body mass index ≥ 30 kg/m^2^; (2) diagnosis of mild or moderate ID [1]; (3) age 25–50 years; (4) medical provider approval to participate in a weight-loss program; (5) has a regular caregiver willing to participate in a support role unless the participant serves as own legal guardian; and (6) has access to a computer with Internet throughout the week. Exclusion criteria include: (1) already participating in a weight-loss program; (2) a medical condition that prevents safe participation; and (3) insufficient capacity to consent.

### Intervention plan

The intervention plan (Fig. 1) was based on a conceptual model that has been previously validated [21]. The POWERS conceptual model combines approaches from other well-established models including the transtheoretical (stages of change model), person-centered theory, and socio-ecological model. The transtheoretical model is utilized at the Problem Identification stage to assess individual barriers, status, and preferences. The POWERS model also utilizes a person-centered approach to identify personal areas of change. The socio-ecological model is used for identifying community-based resources to assist with sustaining health-related behaviors. Starting from the left, the conceptual model begins with problem identification and needs assessment accomplished through a detailed evaluation of the individual’s health status, current activity level, needs and interests, eating behavior, personal and environmental barriers to physical activity, functional ability, and readiness to change. This detailed evaluation is referred to as the Health Appraisal Profile (HAP). The HAP is used to prepare a personalized exercise and nutrition program (middle column of Fig. 1), which includes goal-setting, positive focus, individualized communication and performance feedback, and adapting strategies to help the participant and/or caregiver overcome personal and environmental barriers. Attainment of goals can then be re-evaluated and adjustments made during coached portions of the intervention. The online platform also integrates local community resources, such as accessible exercise facilities and farmers’ markets. Community resources are populated by the POWERS system, the coach, or participant. These resources may assist the participant and their caregiver with accomplishing incremental personal objectives towards long-term maintenance of a healthy lifestyle. Overall, the model illustrates how individuals are guided through problem identification, behavior assessment associated with diet and exercise, and finally, long-term support to improve health and quality of life.

**Fig. 1 Fig1:**
[figure not shown]
POWERS conceptual framework

### POWERS_*for*ID_ platform and website

POWERS_*for*ID_ was customized specifically for adults with ID and is based on the original POWERS system. POWERS_*for*ID_ generates nutrition, exercise, health behavior, health education, and adapted disability-related content from a pre-populated database. Information generated from the participant’s HAP responses is customizable by the health coach. For example, a participant may report low intake of fruits and vegetables due to “dislike of diet and health food.” POWERS_*for*ID_ would then query the database and populate suggestions such as “add fruit to cereal, granola, or yogurt” or “make a fresh fruit smoothie.” The platform also identifies nearby stores where fruits may be purchased and links to a national website that has a smoothie recipe. The health coach also has the ability to freely customize and edit the recommendations (i.e. tips) based on new information and/or participant needs. If additional resources are needed, POWERS_*for*ID_ is able to incorporate local and national resources that may be utilized by the participant and coach. For resources outside POWERS_*for*ID_, links are provided to health resources hosted on the National Center on Health, Physical Activity and Disability’s (NCHPAD) website (www.nchpad.org). An eight-step process for identifying and targeting participant strategies is presented in Table 1.

**Table 1 Tab1:** POWERS process for identifying and targeting participant health behavior strategies

Step	Description
1. Progress monitoring (by coach)	After the initial HAP evaluation, participants can access POWERS to log their progress in terms of weight, physical activity (type, duration, frequency), and diet (calorie intake, fat gram intake, and fruit/veg. servings) anywhere 24/7. During each coaching session, a health coach starts with the review of a participant’s progress since last session. The tracking data are displayed in interactive charts facilitating easy detection of progress or areas of concern. If the target BMI goal is reached, the coaching exercise is complete and the participant is referred to a community-based program; otherwise, the main POWERS steps below will be implemented. If the participant has significant health risk issues that are identified during monitoring, the participant will be advised to contact his/her physician.
2. HAP updates (by coach)	A health coach and a participant work together on the phone to update the HAP, a comprehensive assessment tool that includes a participant’s disability status (e.g. health conditions and functional ability), behaviors (e.g. physical activity, nutrition, screen time), and barriers to achieving diet and physical activity health promotion goals (e.g. separated into intrapersonal, interpersonal, community, and organizational barriers).
3. Objective selection (by POWERS)	A large set of “rules,” developed specialists in nutrition, exercise, health behavior, health education, and disability, are used to associate each wellness objective with specific disabilities, demographics, health issues, and a variety of conditions assessed in HAP. When one or more of these HAP conditions is met, the associated objectives are triggered and presented to the coach. For instance, if an adult participant has a BMI ≥ 30, the objectives of “lower calorie intake,” “increase physical activity,” etc. will be triggered because they are associated with the conditions “adult” and “BMI ≥ 30.”
4. Objective calibration (by coach)	The recommended wellness objectives from Step 3 are generic in nature. They need to be refined and calibrated to accommodate the special needs for the participant and be “measurable.” For instance, it is difficult to quantify the progress against a generic objective such as “lower calorie intake.” Instead, the coach and the participant should work together to set a more measurable objective such as “lower calorie intake to 2000 calories per day in 4 weeks.”
5. Strategy selection (by POWERS)	Similar to how wellness objectives are recommended from the POWERS knowledge base, strategies to achieve these objectives are also available in the POWERS knowledge base and triggered by matching HAP conditions. For instance, if “increase intake of fruits/vegetables” is selected as the wellness objective and the participant has indicated “dislikes diet or health food” as a nutrition barrier in HAP, strategy recommendation such as “add fruit to cereal, granola, or yogurt” and “make a fresh fruit smoothie” will be triggered.
6. Strategy enrichment (by POWERS)	POWERS further “enriches” the recommended strategies by providing a set of wellness education resources (both text materials and videos) to help implement the recommended strategies. These NCHPAD educational resources are associated with strategy recommendations in POWERS via keyword searches, instead of directly linked to the strategies, to provide the flexibility for NCHPAD staff to update these educational resources independently of the POWERS operations.
7. Strategy localization (by POWERS)	POWERS can also propose local community resources to help implement a specific wellness strategy. For instance, when proposing to play golf as a way to increase physical activities, POWERS can automatically search in its community resource database for golf courses that have accessible golf carts based on the locations (e.g. home, work, school, etc.) provided by the participant in HAP. POWERS can then display them on a Google Map using Google Map API. To allow POWERS coaches at local communities to maintain and share the information about these local resources themselves, POWERS allows coaches to submit information about these local resources and the system can automatically process them, including geocoding, to make them accessible to Google Map.
8. Strategy calibration (by coach)	Similar to how wellness objectives are calibrated for individual participants, strategies are refined and calibrated to be measurable and realistic. Instead of using the generic system-generated strategies such as “make a fresh fruit smoothie,” the telehealth coach and the participant could revise it to “make 2 fresh fruit smoothies every week” as the actual strategy. Also, note that Steps 6 and 7 above could provide additional support information to help implement the strategy, such as possible recipes from Step 6 and where to buy the ingredients from Step 7 on a map.

### POWERS_*for*ID_ website

POWERS_*for*ID_ includes a multifocal tailored website designed to facilitate improvements in physical activity and nutritional barriers. The website provides each participant with a personal space to monitor and track health related behaviors. The website also provides discussion boards to interact with a health coach and individualized tips for overcoming nutrition- and physical activity-related barriers. Each participant receives a unique username and login for the website. Once a participant is logged in, he/she sees an overview page that presents the latest message from the health coach as well as information related to weight-loss progress, physical activity goals, and nutrition goals. The participant also has access to areas focused on specific health behaviors. Specifically, there are separate sections in POWERS_*for*ID_ to track water consumption, food intake, and physical activity. Each of these pages reflects the participant’s overall progress towards a daily goal and displays weekly measures of progress. In addition, each page has specific tips for the participant and utilization of these tips as described in Table 1. The participant may also record daily behaviors in the “journaling” section. The health coach has the ability to view information logged by the participant. The coach may also make notes that are not viewable to the participant. These notes may serve as a reference for phone sessions between the participant and coach. A screenshot and description of the POWERS_*for*ID_ main page is presented in Additional file 1.

### Feedback on POWERS_*for*ID_

Qualitative feedback was obtained from five adults with ID and their caregivers over a six-week period. The original POWERS_*for*ID_ diet protocol emphasized a low carbohydrate diet, which has been demonstrated as effective for weight loss and loss of fat mass [27]. However, caregivers repeatedly emphasized difficulty with tracking carbohydrate intake for adults with ID. Caregivers also expressed concern that attempts to reduce carbohydrate intake intruded on the adult with ID’s autonomy. Based on this feedback, a targeted food system was piloted and implemented in place of carbohydrate tracking. The targeted food system utilizes information from a food frequency questionnaire and motivational interviewing techniques to allow the participant with ID to identify foods and dietary strategies he/she is willing to target and improve upon. The targeted food system also simplifies diet-related behaviors by shifting emphasis to only two to five targeted foods instead of relying on total carbohydrate intake. Other changes included simplification of the POWERS_*for*ID_ interface, specifically by eliminating information displayed in line graphs and instead utilizing a traffic light graphic to categorize foods. Infrastructure improvements were also implemented to increase usability for the health coach.

### Intervention

The study design is a 24-week RCT to assess the efficacy of POWERS_*for*ID_ on weight loss and overall health status (target sample: n = 70). The primary aim of this study is to test the feasibility and efficacy of the POWERS_*for*ID_ intervention in obese adults with ID. With a moderate effect size of 0.62 and a two-sided alpha of 0.05, a sample size of 35 participants per group will achieve a power of 0.80. After consent, all participants complete baseline measures and are then randomized to one of two conditions: (1) POWERS_*for*ID_ intervention; or (2) control. De-identified patient demographic data were used to conduct simulation checks to ensure balanced group allocation and to determine a proper randomization protocol. Simulation checks accounted for age, race, and ethnicity. After the simulation checks, a simple randomization sequence was developed. Each individual randomization assignment was then sealed in an envelope. Participants have equal probabilities of randomization to the intervention or control group. When it is time to randomize a participant to either arm, the health coach opens the next envelope in the sequence to reveal the group assignment. Participants are recruited, enrolled, and randomized by the health coach; all other research staff have been blinded to randomization. Participants randomized to the control group receive usual care from the clinic and related clinic staff. In addition, during the 24-week intervention, control group participants complete assessments at baseline, and at weeks 6, 12, and 24. Upon completion of the study period, control group participants are provided educational materials from an online information and resource center specializing in health and disability, as well as the option to contact a toll-free number and speak with an information specialist for further advice on physical activity and nutrition.

Participants randomized to the intervention group receive access to the POWERS_*for*ID_ website and review the interface with the health coach. The participant and coach schedule an initial phone call to review strategies to improve physical activity and diet. Subsequent phone calls occur weekly until the 12th week of the intervention and biweekly during weeks 13–24. All participants visit the clinic at baseline and at weeks 6, 12, and 24. The study protocol is summarized in Fig. 2 (based on SPIRIT 2013 guidelines).

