### Outcomes

Outcome measures and timing of administration are listed in Table 2. Clinic visits include routine care, the HAP, and measurement of body weight and body composition (via waist circumference and bioelectrical impedance analysis). Blood samples for measurement of lipids and blood sugar are collected at baseline and week 24. Participants will be required to visit their medical provider at baseline and weeks 6, 12, and 24. During the visits, participants will receive medical supervision that mimics the routine care provided by the clinic. Routine care consists of measuring a patient’s blood pressure, 0_2_ saturation, urinalysis, height, weight, and waist circumference. Medical records will be accessed to collect the participant’s blood sample results. For the POWERS_*for*ID_ intervention clinicians will also measure body composition via bioelectrical impedance analysis and waist circumference. Standard procedures for assessing anthropometrics, such as removal of additional clothing items, measuring from between the lowest rib and iliac crest for waist circumference, will be utilized in line with standardized clinical procedures. The HAP is completed following completion of clinical measures and may be completed with assistance from a caregiver (if applicable) and/or the health coach.

**Table 2 Tab2:** Outcome measures, instruments, and time points

Measures	Instruments	Time point(s)
Adherence	Logs, enrollment metrics, tracking data	Daily
Demographics	Demographics	Baseline
Functional abilities	POWERS_*for*ID_ disability, health and function	Baseline
Body weight	Scale and bioelectrical impedance analysis of body composition	Clinically measured at baseline and weeks 6, 12, and 24
Physical activity behaviors	Physical Activity and Disability Scale; Barriers to Physical Activity and Disability Scale; Exercise Perception Scale; Self-Efficacy Related to Exercise for People with DD Scale	Baseline and weeks 6, 12, and 24
Physical activity	Physical activity points and steps (pedometer)	Daily
Barriers to PA	Barriers to Physical Activity and Disability Scale	Baseline, weekly, 24 weeks
Nutritional behaviors	Block Food Frequency Questionnaire; Fruit and Vegetable Self-Efficacy Scale; Fruits and Vegetables Outcomes Expectancy Scale; Barriers to Fruits and Vegetables Scale	Baseline and weeks 6, 12, and 24
Nutrition	Healthy eating points	Daily
Dietary barriers	POWERS_*for*ID_ dietary barriers	Baseline and weeks 6, 12, and 24

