### Data analysis

Data analysis is performed by a project coordinator and statistician who are blinded to the intervention group assignment. Participant attrition, session attendance, and instrument completion are recorded and analyzed using descriptive statistics. We hypothesize that by the end of the study, 70% of the participants will be retained, 70% will participate in all coaching sessions, and 100% will have completed at least 80% of the survey instruments at each data collection point. Data will be analyzed with mixed effects models to assess the effect of POWERS_*for*ID_ on participant outcomes. A mixed model is a generalization of the standard linear model that permits repeated measures data to exhibit correlation and non-constant variability over time. We will use each outcome as a time-varying dependent variable and group (POWERS_*for*ID_ vs. control) as main fixed effects. Baseline demographics will be entered as time-invariant covariates if baseline group differences are observed. Intercept will be modeled as random effects. We hypothesize that the trajectory slope of participant outcomes will be more favorable in the POWERS_*for*ID_ group compared to the control group, which will result in a significant GroupXTime interaction effect. We will analyze our data using both on-treatment and intent-to-treat approaches. Participants lost through attrition will be compared on demographic and prognostic variables to those who remain in the study to examine the sample representativeness and potential treatment bias.

Qualitative data analysis from the POWERS_*for*ID_ study results will address motivational interviewing applications, barriers, and successes of the intervention. We will perform thematic analysis using ATLAS.ti software. Thematic analysis is an iterative process that involves the researcher as the instrument for: (1) coding qualitative data; (2) cross-comparing codes for pattern identification; (3) grouping codes into broader themes; and (4) interpreting thematic relationships [31, 40]. We will also report on the level of data saturation achieved.

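### The stated power of 0.80 does not follow from its inputs: d = 0.62, 35 per group and two-sided alpha 0.05 give about 0.72, with no allowance for the expected 70% retention

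*Protocol article*

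**What the plan says.** The sample size statement is in the Intervention section of the protocol article. It begins "With a moderate effect size of 0.62" and continues with a "two-sided alpha of 0.05, a sample size of 35 participants per group will achieve a power of 0.80". The same section gives the overall size as "target sample: n = 70" and says that allocation to the two arms is equally likely. For this calculation it names no test, outcome, correlation, covariate adjustment or dropout allowance.

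The Data analysis section hypothesises that "70% of the participants will be retained" by the end of the study. It plans mixed effects models with a random intercept, tests the group-by-time interaction, and analyses the data both by intention to treat and on treatment.

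**The concern.** The sentence gives effect size, alpha, sidedness, group size and power. Any four of these determine the fifth for a standard two-group comparison, and here they do not agree. Separately, twice 35 is 70, so the power is computed as if every randomised participant contributed a final value, while the plan itself expects about three in ten to be lost.

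The Intervention section makes efficacy part of the primary aim, and the Data analysis section predicts a significant interaction. Readers will use the stated power to judge what a non-significant result means. If the true type II error at the assumed effect is nearer 28% than 20%, and possibly higher after attrition, such a result says less against the intervention than the protocol implies.

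**Working it through.** **Inputs.** From the Intervention section: d = 0.62 (taken as a standardised mean difference, SD = 1), n = 35 per group, two-sided alpha 0.05, stated power 0.80, 1:1 allocation. From the Data analysis section: retention 70%.

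**1. Attempt to reproduce 0.80.**
- Noncentrality = d × √(n/2) = 0.62 × √17.5 = 2.594.
- Normal approximation: Φ(2.594 − 1.960) = Φ(0.634) = 0.737.
- Two-sample t-test (noncentral t, 68 df): 0.725.
- A rank test with relative efficiency 0.955 gives about 0.70.

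None gives 0.80. The shortfall is 6 to 8 percentage points for the two comparisons of means, too large for rounding. Type II error by the t-test is 1 − 0.725 = 27.5%.

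**2. What would give 0.80.**
- Group size at d = 0.62: 2 × (1.960 + 0.842)² / 0.62² = 40.8, so 41 per group. The t-test needs 42 (power 0.802).
- Effect at 35 per group: (1.960 + 0.842) × √(2/35) = 0.67 by the normal approximation, 0.68 by the t-test.

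**3. Retention.** 0.70 × 70 = 49 participants, or 24.5 per group. Power for d = 0.62 if only completers are compared:

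| Completers per group | t-test | Normal approximation |
|---|---|---|
| 24 | 0.557 | 0.574 |
| 24.5 | 0.566 | 0.583 |
| 25 | 0.575 | 0.592 |

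The effect detectable with power 0.80 at 24.5 per group is 0.82 by the t-test (0.80 by the normal approximation).

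**4. Could an unstated gain in precision explain 0.80?** These are assumptions; the article gives no correlation.
- Adjusting for baseline with correlation r multiplies the effective d by 1/√(1 − r²). At 35 per group, normal approximation, power is 0.776 for r = 0.3, 0.808 for r = 0.4 and 0.850 for r = 0.5. By the t-test, 0.80 is reached when 0.62/√(1 − r²) = 0.679, which gives r of about 0.41.
- Averaging three post-baseline visits with between-visit correlation ρ multiplies the variance by (1 + 2ρ)/3. At 35 per group, normal approximation, power is 0.826 for ρ = 0.7, 0.796 for ρ = 0.8 and 0.766 for ρ = 0.9.
- With 24.5 completers per group, baseline adjustment reaches 0.80 only when r is about 0.65 (0.62/√(1 − r²) = 0.817).

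**The case against.** The strongest reply is that the planned analysis is not a two-sample t-test. Weight is measured at four visits and analysed with a repeated-measures mixed model, and step 4 shows that moderate, plausible correlations bring power to 0.80 at 35 per group. A journal article may also leave such detail to a fuller document. This stands to the extent that a valid calculation may lie behind the figure. It does not rescue the sentence as printed, which gives a complete set of inputs with an output they do not produce. A calculation that used a correlation needs that correlation stated, so the text changes either way.

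The second reply concerns retention. A participant who drops out after week 6 or week 12 still contributes those weights to the mixed model, so a completers-only figure overstates the loss. That stands in full. A reader might take 0.57 as the trial's power, but the documents do not support that reading. It is one scenario, under an analysis that differs from the planned mixed model.

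A reader might also infer that a one-sided alpha of 0.05 was used by mistake. This is conjecture. One-sided power at 35 per group is 0.82, which does not match 0.80 either, and the text says two-sided.

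Finally, the study has feasibility aims, for which power matters less. But the Intervention section names efficacy alongside feasibility as the primary aim, so the stated power has to be right.

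**Conclusion.** The point holds as an inconsistency in the printed figures. On the plain reading, a comparison of two means with d = 0.62, power is 0.725 (t-test) or 0.737 (normal approximation) against 0.80 stated. This does not depend on attrition. The lack of any allowance for the plan's own 70% retention is a second, separate weakness. Its size is less certain: about 0.56 to 0.57 is the completers-only t-test figure, and the mixed model may do better.

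Two stronger conclusions are not supported. The documents do not show that the trial's power under its planned model is below 0.80, because the correlations that would decide this are not given. Nor do they show that attrition could be offset by taking later weights from clinic charts. The Outcomes section does say "Medical records will be accessed to collect the participant", but the sentence goes on to limit this to blood sample results.

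**What to change.** Keep the target of 70 and replace the power sentence with figures that agree, for example:

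> With 35 per group and two-sided alpha 0.05, power is about 0.72 for d = 0.62 and 0.80 for d = 0.68; in a completers-only comparison at 70% retention, power for d = 0.62 is about 0.57.

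If a baseline or repeated-measures correlation was used to reach 0.80, state its value and source and show the power with it, at full and at 70% retention.

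The cost is one or two sentences and, unless a correlation is documented, a less favourable stated power. Recruitment, data collection and the analysis model do not change.
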